## Abstract

**Background:**

Over 10 million newborns worldwide undergo resuscitation at birth each year. Pediatricians may use electrocardiogram (ECG), pulse oximetry (PO), and stethoscope in determining heart rate (HR), as HR guides the need for and steps of resuscitation. HR must be obtained quickly and accurately. Unfortunately, the current diagnostic modalities are either too slow, obtaining HR in more than a minute, or inaccurate. With time constraints, a reliable robust heart rate detector (HRD) modality is required. This paper discusses a protocol for conducting a methods-based comparison study to determine the HR accuracy of a novel real-time HRD based on 3D-printed dry-electrode single-lead ECG signals for cost-effective and quick HR determination. The HRD’s HR results are compared to either clinical-grade ECG or PO monitors to ensure robustness and accuracy.

**Objective:**

The purpose of this study is to design and examine the feasibility of a proof-of-concept HRD that quickly obtains HR using biocompatible 3D-printed dry electrodes for single-lead neonatal ECG acquisition. This study uses a novel HRD and compares it to the gold-standard 3-lead clinical ECG or PO in a hospital setting.

**Methods:**

A cross-sectional study is planned to be conducted in the neonatal intensive care unit or postpartum unit of a large community teaching hospital in Toronto, Canada, from June 2023 to June 2024. In total, 50 newborns will be recruited for this study. The HRD and an ECG or PO monitor will be video recorded using a digital camera concurrently for 3 minutes for each newborn. Hardware-based signal processing and patent-pending embedded algorithm-based HR estimation techniques are applied directly to the raw collected single-lead ECG and displayed on the HRD in real time during video recordings. These data will be annotated and compared to the ECG or PO readings at the same points in time. Accuracy, *F*_1_-score, and other statistical metrics will be produced to determine the HRD’s feasibility in providing reliable HR.

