#### Inclusion Criteria

The inclusion criteria for the PPU infants are as follows:

Corrected gestational age (35 weeks + 0 days)Infants undergoing routine CCHD screening with PO at 24 hours of life or laterStable clinical statusParental consent

For the NICU infants, the inclusion criteria are as follows:

Corrected gestational age (30 weeks + 0 days)Infants undergoing routine 3-lead continuous ECG monitoring or POInfants with at least 24 hours of lifeStable clinical status, as defined by the following: stable requirement for supplemental oxygen and stable respiratory rate on at least 2 measurements, a respiratory rate <70 breaths per minute, HR <180 beats per minute, oxygen supplementation <0.5 L/min via nasal prongs, and not being on heated high-flow oxygenParental consent

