#### Data Analysis

HR and raw ECG data will be analyzed using MATLAB (the MathWorks). Infant demographics will be analyzed using summary statistics. Continuous variables will be expressed as mean (SD) values, and categorical variables will be expressed as numbers (percentages), unless otherwise stated. The HR from HRD will be compared to PO or ECG using a paired *t* test. The Bland-Altman method will be used to compare the HR derived from each device—the HRD and the PO or ECG monitor, used as reference. The correlation between devices will be assessed using Pearson *r* statistic. Data will be first analyzed using all data points available, and outliers will be defined as 20 beats per minute rate difference between the methods. These discrepancies will be further analyzed to find the likely reason for deviation, including reexamination of the video recordings.

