## Discussion

This paper discussed a research protocol for conducting accurate and reliable HR estimation using a novel real-time HRD based on 3D-printed dry-electrode single-lead ECG signals. Recent advances in biomedical sensor and wireless information and communication technologies have enabled us to develop a novel HRD, aimed at potentially disrupting the traditional assessment of HR in neonatal resuscitation efforts. The rapid application, measurement, and display of HR on a device mounted directly on the neonate addresses significant gaps in the provision of optimal neonatal resuscitation. The main objective of this study is to examine the novel HRD’s ability and feasibility in obtaining an accurate HR in newborns, using dry electrodes, and comparing it to the state-of-the-art clinical-grade HR monitors at the hospital.

However, this study is limited to the feasibility of HR detection on a healthy population of newborns using dry electrodes, and it does not cover in-depth analytical metrics of ECG and HR for disease diagnosis. It is apparent that further studies should focus solely on ECG abnormalities in neonates, including bradycardia, pulseless electrical activity, and long QT syndrome. The work is also limited to the use of certain 3D-printed conductive plastic-based dry electrodes for single-lead ECG acquisition, limiting its applicability when ECG quality is compared to other dry-electrode materials, such as stainless steel and textiles. Furthermore, the proposal does not include clinical-grade ECG acquisition for comparison with the HRD’s raw ECG signals due to the restraints in obtaining access to HR monitor raw ECG information. In addition, the use of algorithms on clinical-grade devices cannot be accessed, limiting this work to the examination of HR information between the HRD and clinical HR monitors. However, the raw ECG obtained through the HRD can be used to derive novel hand-crafted features that assist in quick HR estimation and prediction using artificial intelligence.

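### The abstract names F1-score among the measures that decide feasibility, but Data Analysis omits it and nothing defines it for paired continuous heart rates

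*Protocol article*

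**What the plan says.** The abstract (Methods paragraph) describes annotating the displayed heart rates, comparing them with the ECG or pulse oximetry monitor at the same time points, and then: "Accuracy, *F*_1_-score, and other statistical metrics will be produced to determine the HRD’s feasibility in providing reliable HR".

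The Data Analysis section gives a different list:
- a paired t test: "The HR from HRD will be compared to PO or ECG using a paired" t test;
- agreement: "The Bland-Altman method will be used to compare the HR derived from each device";
- correlation: "The correlation between devices will be assessed using Pearson" r;
- a discrepancy flag: "outliers will be defined as 20 beats per minute rate difference between the methods", which leads to re-examination of the video.

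The F1-score is not in that list or anywhere else in the body. Accuracy does recur, in Objectives as a research question and in Study Design as another word for reliability against the clinical monitors, but it is not defined as a rate. Data Management describes the data as numerical heart rates read from both screens every 2 seconds for 3 minutes.

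**The concern.** An F1-score is a classification measure. It needs a rule saying which readings are true positives, false positives and false negatives. The question here is how closely one continuous heart rate agrees with another, and the article supplies no class, no tolerance for a correct reading and no counting rule. The only between-device threshold, 20 bpm, flags readings for a second look and does not define correctness.

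The abstract therefore names a measure as helping to decide feasibility that the analysis section does not plan. If the definition is settled once the readings are known, whoever settles it also settles the number, and the same device error can be reported as a noticeably better or worse score.

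**Working it through.** **Inputs from the article.** Readings every 2 s for 3 min in 50 infants (Data Management); 20 bpm outlier flag (Data Analysis); stable infants only (Recruitment, Inclusion Criteria, Exclusion Criteria); a healthy population, with bradycardia left to later studies (Discussion).

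**Reproducing the stated data volume.** 180 s / 2 s = 90 readings per device per infant; 90 × 50 = 4500. This matches the article's approximate figure, read as 4500 pairs.

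**1. Effect of the counting rule.** F1 = 2TP / (2TP + FP + FN). Let p be the share of readings that are correct, so TP = p and misses = 1 − p.
- Misses counted only as FN, or only as FP: F1 = 2p / (2p + 1 − p) = 2p / (1 + p). For p = 0.80, 1.60 / 1.80 = 0.89; for p = 0.90, 1.80 / 1.90 = 0.95.
- Misses counted as both FP and FN: F1 = 2p / (2p + 2(1 − p)) = p, that is 0.80 and 0.90.

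**2. Effect of the tolerance.** The article gives no SD for the differences between devices, so a range is assumed: Normal differences, zero bias, SD 3 to 10 bpm. Then p = 2Φ(tolerance / SD) − 1. Each cell shows accuracy p, then F1 with misses counted once. With misses counted as both, F1 equals p.

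| Assumed SD | 5 bpm | 10 bpm | 20 bpm |
|---|---|---|---|
| 3 | 0.904 / 0.950 | 0.999 / 1.000 | 1.000 / 1.000 |
| 5 | 0.683 / 0.811 | 0.954 / 0.977 | 1.000 / 1.000 |
| 8 | 0.468 / 0.638 | 0.789 / 0.882 | 0.988 / 0.994 |
| 10 | 0.383 / 0.554 | 0.683 / 0.811 | 0.954 / 0.977 |

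At SD 5 and a 5 bpm tolerance, the counting rule alone moves F1 from 0.683 to 0.811.

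**3. Effect of choosing a heart-rate class.** Suppose the positive class were a reference rate below a cut-off. Assume reference rates are Normal with mean 140 and SD 15, and differences have SD 5 (all illustrative; none is in the article). By simulation, for the same device error:
- cut-off 100: F1 0.612, accuracy 0.996;
- cut-off 140: F1 0.897, accuracy 0.898;
- cut-off 160: F1 0.975, accuracy 0.955.

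At 100 the expected share of positives is Φ((100 − 140) / 15) = 0.0038, or about 17 of 4500 readings. If neither device ever shows a low rate, TP = FP = FN = 0 and F1 is 0/0, while accuracy is 100%.

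**The case against.** The strongest reply has four parts.

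- **The abstract's list is open.** It ends with unspecified other metrics, which can cover Bland-Altman. No metric is labelled primary and no success threshold is attached to F1. This stands: a reader might infer that feasibility rests on F1 alone, and the text does not say so.
- **F1 can be computed.** A reader might infer that the design rules it out. It does not. F1 makes no use of true negatives, so their absence is no obstacle. A wrong displayed rate and a missing display are workable candidates for the error cells, and Data Collection already has a 60-second device-failure rule. Nor is a beat-level score excluded by the Discussion's statement that "the proposal does not include clinical-grade ECG acquisition for comparison with the HRD’s raw ECG signals": the device's own 500 Hz ECG is stored and could be annotated. Such a score would not, however, test agreement with the reference monitor, which is what the abstract's sentence is about.
- **Accuracy belongs in the abstract.** It is a stated research question, and the agreement analysis addresses it. This stands; only F1 lacks any support in the body.
- **A condensed article may leave definitions to a fuller document.** This is true of detail. But Data Analysis does list the methods, its list differs from the abstract's, and the added item is a classification score applied to a continuous-agreement question. That is a mismatch in the text as printed.

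On low rates, the eligibility line "a respiratory rate <70 breaths per minute, HR <180 beats per minute" is an upper limit for NICU infants and says nothing about how often low rates occur. The expectation of few positives rests on the stability criteria and on the Discussion's description of a healthy population.

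**Conclusion.** The point holds as a mismatch between sections and a missing definition. The abstract names the F1-score among the measures that determine feasibility; Data Analysis does not plan it, and nothing in the article fixes what it would mean for these readings. The size of the ambiguity from the counting rule alone is 0.89 against 0.80 at 80% correct and 0.95 against 0.90 at 90% correct, and this arithmetic needs no assumption about the device. The dependence on tolerance and on class cut-off is larger, but those figures rest on assumed SDs and an assumed heart-rate distribution and show sensitivity only.

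Neither counting convention is in the article, so the figures do not show that the investigators will report an inflated score. They show that the score has no fixed meaning until a rule is set in advance.

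**What to change.** Drop the F1-score from the abstract, keep accuracy, and have the abstract and Data Analysis name the same feasibility measures:

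1. Bland-Altman bias and limits of agreement, calculated to allow for repeated readings within infant.
2. Accuracy, defined in advance as the percentage of scheduled readings within a pre-set tolerance of the reference, with confidence intervals that treat the infant as the unit and with missing displays counted as not within tolerance. The existing 20 bpm difference could serve as one cut-off. Under the assumed SDs of 3 and 5 bpm it gives 1.000, so a tighter cut-off alongside it, also fixed in advance, would be more informative.

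Add a sentence stating that classification of low heart rates cannot be assessed in this population.

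The repeated-measures limits, the within-tolerance percentage and the infant-level intervals are not in Data Analysis now, so this is more than a wording change. The cost is a little extra analysis of readings that are already to be collected, with no new data.

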**Results:**

The study is ongoing. The projected end date for data collection is around July 2024.

**Conclusions:**

The study will compare the novel patent-pending 3D-printed dry electrode–based HRD’s real-time HR estimation techniques with the state-of-the-art clinical-grade ECG or PO monitors for HR accuracy and examines how fast the HRD provides reliable HR. The study will further provide recommendations and important improvements that can be made to implement the HRD for clinical applications, especially in neonatal resuscitation efforts. This work can be seen as a stepping stone in the development of robust dry-electrode single-lead ECG devices for HR estimations in the pediatric population.

**International Registered Report Identifier (IRRID):**

DERR1-10.2196/45512

## Introduction

### Background

Each year, over 10 million newborns require resuscitation worldwide, representing more than 10% of all global births [1]. Neonatal resuscitation is the set of interventions at the time of birth to support the establishment of breathing and circulation. These interventions include providing warmth to the infant using a heat source, placing the head in a sniffing posture with neck flexion and upper cervical extension (a position to open the airways), drying the infant, and simulating breathing. Multiple metrics—respiration, infant color, and heart rate (HR)—are measured every 30 seconds to ensure successful neonatal resuscitation [2]. Out of these indicators, HR is identified as the most important for an effective resuscitation process [3]. HR guides decision-making and escalation of care, including positive pressure ventilation, endotracheal intubation, chest compressions, and administration of epinephrine.

Despite the importance of HR in neonatal resuscitation, HR determination is challenging due to a lack of evidence regarding the most rapid and accurate method to assess it. Clinically accepted methods of HR assessment include pulse palpation (umbilical, brachial, and femoral), auscultation with a stethoscope, pulse oximetry (PO) monitoring, and 3-lead electrocardiogram (ECG) monitoring [2]. It is important to note that neonatal resuscitation efforts should be performed within the first minute of life, known as the “golden minute,” to ensure a high success rate and avoid neurodevelopmental disorders and hypoxic injury [4].

A systematic review compared these different methods in terms of expense, intermittent or continuous HR assessment, and other strengths and weaknesses. Auscultation and pulse palpation are rapid and easily accessible approaches due to their low cost. However, both approaches are highly inaccurate and unreliable, resulting in errors of omission, which causes failure or delay in resuscitation steps and commission through inappropriate intervention [5]. Auscultation requires a pause in resuscitative efforts, which can disrupt the flow of resuscitation and result in a delay in stabilization of the newborn. This method is the most used approach compared to other HR determination approaches, due to its quick and easy accessibility as well as its cost-effectiveness. However, auscultation accuracy is reliant on health care professional experience and can be inconsistent from one practitioner to the other, resulting in inequitable care [6]. On the other hand, PO is relatively inexpensive and noninvasive, and it displays continuous HR and oxygen saturation to the entire team in the delivery room. However, a pulse oximeter can be inaccurate due to motion artifact, ambient light, or poor tissue perfusion, and it takes several minutes to apply and achieve the first data display, potentially delaying resuscitative efforts [4,5].

Current guidelines suggest a 3-lead ECG monitor as the gold standard for HR determination in neonates due to its high speed and accuracy and because of its capabilities to provide continuous visual and auditory data compared to the other modalities, such as PO and auscultation. However, 3-lead ECG has its disadvantages. Errors in the placement of the 3 leads can yield inappropriate ECG signals that cannot be used for HR detection [7]. Additionally, similar to PO, wet electrode ECG placement takes time to apply, surpassing the golden minute of life [5]. ECG adhesive wet electrodes can cause skin damage to premature infants. Moreover, motion artifacts may be present with ECG leads. In rare scenarios, ECG-derived HR may fail to correspond with the effective mechanical contraction of the heart [8]. Most importantly, both PO and 3-lead ECG require additional equipment, which needs to be purchased and maintained, accumulating significant expenses for health care systems [7,8]. Both technologies may not be feasible or accessible in areas with limited health care resources [9].

Recent rapid scientific advancement in sensing technology have driven the development of novel technologies to assess HR, including camera-based photoplethysmography, reflectance PO, laser Doppler technology, capacitive sensors, piezoelectric sensors, electromyography, and electronic or digital stethoscope (DS) [10]. Although a systematic review of these novel technologies concluded that none are ready for widespread clinical adoption, DS offers the greatest potential [10]. Currently, DS is at the forefront in the field of “computer-aided auscultation,” as advances in acoustic sensor design, digital signal processing and filtering, auditory enhancement, and machine learning can enable automated diagnoses of cardiac dysfunction [10,11]. In neonates, DS used for HR measurement is more accurate than auscultation or pulse palpation and faster than PO in “time to first HR display”; DS also correlates appropriately with ECG HR in noncrying infants [10-12]. Furthermore, DS is most similar to existing smart device technologies that are rapidly adopted, in both high- and low-resource settings. These technologies include smartphones, wearables, and other devices in the Internet of Medical Things. Although DS represents a significant improvement in neonatal resuscitation HR monitoring, further refinement and evaluation is necessary before clinical implementation, along with optimization of the existing technologies in a user-centric manner [13]. DS has severe disadvantages, including short battery life, low clinical adoption due to training requirements [14], and its nonstandardized variable sensor technologies, such as the differences between Littman Eko DUO with an ECG module, Littman CORE with analog and digital amplification, and Thinklabs’ One DS with a nonstandard headphone jack. It is important to note that none of the current DS technologies take neonatal ECG into consideration during their development.

It is evident there is a lack of cost-effective and fast signal acquisition technology that uses the gold-standard ECG for quick HR measurements and display in newborns. This study focuses on the deployment of a single-lead ECG handheld monitor capable of using dry-electrode ECG for signal acquisition and HR measurements in a quick and efficient manner. The following protocol study is structured as follows: the study significance, its impact on the current technologies in single-lead ECG devices for neonatal HR monitoring, and the objectives of this study. The Methods section is presented next, and it covers an in-depth look into the ethics-approved protocols through Study Design, Study Personnel, Recruitment, Inclusion and Exclusion Criteria, Ethical Considerations, and Study Procedures sections. Study Procedures section includes the subsections of Data Collection, Debrief, Data Management, Data Analysis, and Data Maintenance and Security. These sections are followed by the Results section, which offers the current progress of this study. Lastly, the final section provides a brief discussion of the protocol and the limitations of the current study, providing future steps to further improve neonatal single-lead ECG monitoring.

### Study Significance and Impact

Given that no single method of HR assessment is clearly superior to others, finding the optimal method to delineate HR within the golden minute after birth remains elusive. Pediatric guidelines recognize this knowledge gap and identify the opportunity to develop new technologies for the rapid, accurate assessment of HR after birth, ideally integrating newborn ECG. Currently, there are no novel medical devices that have been specifically developed to provide rapid and accurate HR immediately after birth. The proposed research study will address several gaps in the scientific study of device development, vital signs measurement and monitoring, and neonatal resuscitation. Recent advances in biomedical sensors and wireless communication technologies have enabled us to develop a novel HRD, targeted to outperform the traditional HR assessment in neonatal resuscitation. The rapid application, measurement, and display of HR on a device located on the neonate addresses significant gaps in the provision of optimal neonatal resuscitation. The HRD is undergoing rigorous design and development, and this study aims to assess its feasibility in quickly detecting accurate HRs in infants using 3D-printed dry electrodes. This early proof-of-concept HRD study will establish the basis for using 3D-printed dry electrodes and determine whether novel HR estimation algorithms are appropriate for neonatal HR applications.

### Objectives

The overall aim of this research study is to evaluate a novel HRD that may enable timely and appropriate neonatal resuscitation. This study is being completed using a phased sequential user-centered approach. We completed the first phase of this research to determine end-user requirements and preferences for HR assessment in neonatal resuscitation. This phase resulted in the current design and features of the HRD.

The second phase outlines the creation of the HRD conceptual design and proof-of-concept prototype to be used in the final phase of feasibility mentioned in this study.

In the final phase, the focus of this proof-of-concept research study is to examine the functionality, speed, robustness, and reliability of the prototype HRD.

Specific research questions to be answered through this phase are the following:

How long does it take to place the HRD on an infant?Can the prototype HRD detect the HR of newborns?How fast can the prototype detect the HR of newborns?How accurate is the HR detection when compared to PO or ECG?

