### Recruitment

All Infants admitted to the PPU after routine delivery, regardless of method, and all infants admitted to the NICU will be eligible if their clinical status is stable and not at high risk of deterioration. In total, 50 newborns will be recruited based on previous accepted research studies that focused on examining long-term neonatal ECG and HR monitoring applications using proof-of-concept novel ECG acquisition devices [14-19].

The two groups of infants are identified as follows:

Infants admitted to the PPU who are at least 24 hours of age and are undergoing routine critical congenital heart disease (CCHD) screening with PO.Infants admitted to the NICU who are routinely placed on 3-lead ECG or PO monitors.

Recruitment steps include the following:

Infants will be identified by a pediatrician for eligibility 5 days a week (Monday to Friday) between 8 AM and 8 PM. Recruitment on Saturday and Sunday will be done if feasible. Recruitment will happen on random days when a pediatrician is available and time permits.

Once an infant is identified based on eligibility (ie, inclusion and exclusion criteria), mentioned below, the pediatrician will ask the bedside nurse to ask the parents if they would be willing to speak to the pediatrician as shown in the recruitment script in Multimedia Appendix 1.

The pediatrician will then meet the parents in a face-to-face meeting to discuss the study, provide the written consent form, and potentially obtain consent. The parents will be given at least 15 minutes to review the consent form prior to being asked to sign it. When the parents are not available at the bedside, the pediatrician will inquire the nurse about a suitable time for the parents to meet. The infants will not be under the care of the researcher pediatrician as their primary admitting health practitioner to avoid a conflict of interest.

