### Study Procedures

The PPU infants will be placed in the supine (face up) position. The conventional PO will be connected to the right hand as per the device’s instructions and CCHD screening protocol. In the usual standard of care for CCHD screening, PO is placed on the right hand and right or left foot for 1 to 2 minutes. The change in the standard of care will include the data collection protocol during the time of CCHD screening, which includes video recording of the HRD and PO simultaneously. The HRD will be held in place by a pediatrician on the thorax for 3 minutes. This will prolong CCHD screening by an additional 1-3 minutes. On the other hand, as per the usual standard of care, NICU infants will be placed in the supine (face up) position prior to their usual feeding time; they will be unbundled and have their diaper changed. An already attached conventional 3-lead ECG will be placed on the infant’s chest, as per the conventional 3-lead ECG device’s instructions. The change in this standard of care will involve the thorax to be exposed, if not already exposed, and the HRD will be held in place by a pediatrician on the thorax for 3 minutes during simultaneous video recording of the HRD and the 3-lead ECG monitor. It is important to note that the 3-lead ECG electrodes will not be in contact with the HRD’s dry electrodes.

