#### Data Collection

The displayed HR from the HRD and the PO or ECG monitor will be video recorded for 3 minutes within the same video frame, as shown in Figure 1. Video recording will take place using a dedicated research digital camera mounted on a stand. Video recording will start once the infant is settled and the PO or ECG readings are stable. Stable readings are defined based on the device’s instructions on waiting for an appropriate amount of time after sensor placement for clinical HR determination. The HRD will then be placed on the infant’s chest until a consistent HR is displayed for 3 minutes, at which point video recording will start. After 3 minutes, the HRD will be removed, and then, the recording will be stopped. After the recording is completed, the entire HRD, including electrodes, will be wiped down with a surface disinfectant towelette (CaviWipe; Metrex). HRD device failure will be considered if no HR is displayed on the HRD within 60 seconds of application to the thorax.

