#### Data Management

Video recordings will be individually analyzed by 2 health professional researchers to determine the time it takes to apply the HRD to the thorax and the time from HRD placement to a steady HR display. Each researcher will review and record the HR from the HRD and PO or ECG at 2-second intervals for 3 minutes, providing approximately 90 HR notations per device per patient. For 50 newborns, the total number of HR annotations will be approximately 4500 data points. This will result in multiple HR data points to compare. To avoid human error in the annotation process, discrepancies in the HR of more than 5 beats per minute between the 2 researchers will lead to a reexamination of the video recordings until a consensus can be reached regarding the correct HR. The annotations from the 2 researchers will be averaged for the subsequent analyses.

Additionally, the HRD will record raw ECG signals for the duration of the device being in contact with the infant. Raw ECG data will be collected at 500 Hz sampling rate and transmitted to a research-dedicated laptop. The raw ECG and HR information from the HRD will be stored on different CSV files with a randomized identification number.

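### Robustness is a stated focus, but recording starts only in settled infants and infant state is not coded, so the plan supports agreement mainly in calm, stable newborns

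*Protocol article*

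**What the plan says.** The Objectives section lists robustness beside functionality, speed and reliability ("examine the functionality, speed, robustness, and reliability of the prototype HRD"). The Abstract links the word to the comparison with clinical monitors: "The HRD’s HR results are compared to either clinical-grade ECG or PO monitors to ensure robustness and accuracy". No section defines it. The four research questions cover placement time, ability to detect, speed and accuracy. Study Design names the same four and equates reliability with accuracy.

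Data Collection gives two start conditions. First: "Video recording will start once the infant is settled and the PO or ECG readings are stable". Shortly after, recording is instead set to begin later: "The HRD will then be placed on the infant’s chest until a consistent HR is displayed for 3 minutes, at which point video recording will" (the sentence closes on that beginning). Eligible infants are clinically stable, and for NICU infants the entry criteria include a heart rate below 180.

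Under Data Management, two researchers read both displays "at 2-second intervals for 3 minutes, providing approximately 90 HR notations per device per patient". Besides the two timings taken from the video, heart rate is all they are said to record. Data Analysis uses all available points first, then defines outliers as differences of 20 beats per minute and looks for their cause, including on the video. The Discussion limits the work to healthy newborns and defers disease diagnosis. It does not mention the settled start.

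**The concern.** The article itself identifies movement as a threat to heart-rate devices. In the Background it says that "a pulse oximeter can be inaccurate due to motion artifact, ambient light, or poor tissue perfusion", that ECG leads can also show motion artifact, and that the digital stethoscope tracks ECG in infants who are not crying. A reader will therefore take a robustness result to include some tolerance of these conditions. Yet each recording begins at the point where they are least likely, and any movement that follows is not marked in the data.

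If errors are commoner during movement, the pooled agreement will look better than agreement under movement. Nothing in the planned output would let a reader separate the two. The Conclusions and Discussion promise recommendations and improvements to the prototype. Information on when the device loses or misreads the heart rate is what those would need most.

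**Working it through.** **1. The plan's own figures.** 3 minutes = 180 s; 180 / 2 = 90 notations per device per infant; 90 × 50 = 4500. Both stated figures reproduce. The 50 cannot be re-derived: "In total, 50 newborns will be recruited based on previous accepted research studies", with no precision target or power calculation given. No stated figure bears directly on robustness.

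**2. The two start conditions.**
- The first condition is a settled infant and a stable reference; the HRD is placed afterwards. Recording can then include placement and the first seconds of display.
- Under the second, the HRD is already on the chest and showing a consistent value when recording begins. An infant in whom the HRD never reached that state would not be recorded.
- Data Management takes the time to apply the HRD, and the time from placement to a steady display, from the video. Only the first order of events allows this.

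The two sentences must be reconciled. The second also conditions the agreement data on the HRD already working.

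**3. Does the settled start exclude movement?** No. It governs the start only. The device is hand-held for the next 3 minutes, and the NICU infants are being handled around that time ("NICU infants will be placed in the supine (face up) position prior to their usual feeding time; they will be unbundled and have their diaper", in the words of Study Procedures). The heart-rate limit of 180 is an entry criterion, not a cap during recording. No rule removes frames with movement or crying. Such episodes are possible, but their number is left to chance.

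**4. How many might occur?** The documents give no rate, so the share q of infants with an episode during recording is assumed. Expected number = 50q; the tail probabilities come from a binomial distribution with n = 50.

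| q (assumed) | Expected infants | P(at least 5) | P(at least 10) |
|---|---|---|---|
| 2% | 1 | 0.003 | 0.000 |
| 5% | 2.5 | 0.104 | 0.000 |
| 10% | 5 | 0.569 | 0.025 |
| 20% | 10 | 0.982 | 0.556 |
| 30% | 15 | 1.000 | 0.960 |

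At q = 10%, 5 infants supply at most 5 × 90 = 450 of the 4500 frames, and fewer if an episode fills only part of the recording. Frames from one infant are also correlated, so the information is closer to 5 infants than to 450 frames.

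**5. What the outlier review can give.** The error rate under movement is (moving frames with a large difference) / (all moving frames). The review could supply the numerator. The denominator is never counted, because frames without a large difference are not classified. Movement during which the HRD read correctly is the best evidence for robustness, and it goes unrecorded. The 60-second failure rule concerns the first display only, not a display lost later.

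**The case against.** The strongest reply is that this is an early proof of concept. Study Design places the resuscitation use in later versions and studies. Since movement disturbs both references, a settled start protects the comparator: without a sound reference, a disagreement cannot be attributed to the HRD. This stands, and it is why the settled start should be kept. Dropping it would also change an ethics-approved procedure.

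A second reply is that robustness is one word in a list, with no research question behind it, and that the Abstract equates it with agreement. This stands in part. But on that reading it adds nothing to reliability, which the Objectives list separately, so the article should either define it or stop using it.

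A third reply is that a full protocol or analysis plan could hold a by-state analysis. That is possible, and the absence of a table alone would not be a point. The concern rests on what the article does fix: when recording starts, what is annotated, and which limitation is stated.

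A reader might infer more: that movement and crying are removed from the data, that infants who do not settle are never recorded, or that robustness cannot be addressed at all. The documents do not support these readings. The condition applies only at the start and has no stated time limit on waiting. Later frames are kept, and large differences are traced on the video. Nor can a multiple be put on any understatement of error, since every input to it would be assumed.

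**Conclusion.** The point holds in a limited form. The start conditions select against movement and crying, infant state is not marked, and all frames are pooled. As planned, the study supports agreement mainly in calm, stable newborns, and the stated limitation does not say so. The accuracy estimate for those conditions remains usable in this respect.

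The size of any bias is unknown. Its direction rests on one assumption, that HRD errors are commoner during movement. The counts of infants with an episode rest on assumed rates of 2% to 30%. The conflict between the two start conditions needs no assumption; it is in the text.

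**What to change.** - **Data Collection:** keep the settled start. Reconcile the two start conditions so that recording does not depend on the HRD already showing a heart rate.
- **Data Management:** have the two researchers code infant state at each 2-second point they already read, as still or as moving/handled. Code crying only where the picture, sound or a live note allows; the article guarantees only that both displays share the frame. Flag frames with a degraded reference.
- **Data Analysis:** report agreement and loss of HRD display by state and by the reference heart-rate range actually observed.
- **Wording:** use robustness only for the by-state result; otherwise drop the word.
- **Discussion:** state that recordings began in settled, clinically stable infants, and that no estimate exists for states or heart-rate ranges not observed. Replace the description of the sample as healthy with the enrolled population, since the Inclusion Criteria admit NICU infants from 30 weeks' corrected gestational age, some on supplemental oxygen.

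**Cost:** somewhat more annotation and one more table. Moving frames will probably be few, so their intervals will be wide, and some will have an unreliable reference. The by-state figures may look less favourable than the pooled one.
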